**Figure 1 F1:**
[figure not shown]
Formulas for calculating the QALYs gained in the first and last six months after the beginning of the program.

In the Figure 1, d_0–6 _is the incremental treatment effect on change in EQ-5D utility score for the first 6 months and d_6–12_the incremental treatment effect on change in EQ-5D utility score for the last 6 months. These incremental treatment effects will be estimated using multivariate ordinary least squares regressions, adjusting for baseline differences among treatment groups. The covariates included in the models will be: age, gender, years of education, employment and marital status, baseline FIQ and EQ-5D utility scores, and type of medication prescribed. To address uncertainty in the ICUR sampling distribution, non-parametric bootstrapping with five thousand replications will be carried out for each treatment comparison [29].

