### Setting and study sample

Three primary health care centres (Viladecans-2, Gavà-1 and Gavà-2) in the province of Barcelona (Catalonia, Spain) voluntarily participated for the study. The sample pool (n = 530) comprises only those patients included in a FM database of the Viladecans Hospital for the years 2005 and 2006. In the event of a lack of participants, the plan is to recruit patients with FM included in the database during the year 2007.

Patients considered for inclusion will be those aged 18–75 years-old, contactable by telephone, who meet the diagnostic criteria of FM established by the ACR. The following patients will be excluded: those with a diagnosis not based on the ACR criteria, those with cognitive impairment or suffering from physical, mental/psychiatric limitations or a severe concurrent rheumatologic illness that impedes participation in the study evaluations, those who are not expected to live at least 12 months and those without schooling.

To calculate the sample size it was taken into account that we need to obtain a difference of at least 5 points in the FIQ between those that respond and those who are resistant to the intervention. The criterion of 5 points is based on two previous studies conducted with Spanish fibromyalgia patients [21,22]. A total of 109 patients per condition is needed to conduct the study, assuming an alpha risk of 0.05 and a beta risk of < 0.20 in a bilateral contrast, a standard error of 12.1 reported in a previous study [21], and a 15% dropout rate.

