### Data collection and ethical aspects

First, patients that meet the inclusion criteria will be phoned by a research assistant who is a psychologist. Second, the research assistant will make an appointment with those patients that agree to participate in the study. Third, written consent will be obtained before the beginning of the study. Participants will be provided with a general overview of the aims and activities of the study. They will be also informed that they may choose to drop out at any time with the guarantee that they will continue to receive the treatment considered most appropriate by their physician. Patients in the control group will receive the treatment considered most appropriate by their physician.

Results will be monitored and most of data collected by means of standard questionnaires conducted in face-to-face interview by the research assistant, who has been trained in the administration of the instruments. The research assistant does not know which study group the patients being interviewed belong to ("blind"). Follow-up assessments shall take place at 1, 2, 6 and 12 months after the inclusion of the patient (see Table 1).

**Table 1 T1:** Follow-up assessments.

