### Intervention program

Participants from the intervention group will undergo a multi-component psycho-educational program that deals with FM based on available scientific evidence. It includes measures and instruments that can be employed within the Catalan Primary Health Care, whereas the participants from the control group will receive only the treatment prescribed by their physician.

The intervention program consists of nine 2-hour sessions delivered during a two month period. Participants will be allocated in groups with a maximum of 18 subjects per group. All sessions will take place at the PC centres Gava-2 or Viladecans-2. The contents of each session are displayed in Table 2.

**Table 2 T2:** Summary of the intervention program.

**Session 1: **General information. Expectations of the patients. History of the illness. Principal and secondary symptoms in FM. Physiological mechanisms involved in the genesis of pain.
**Session 2: **Relaxation training-I
**Session 3: **Diagnosis. Pharmacological and non-pharmacological treatments. Prognosis. Current model of health care in Catalonia. Units specialized in the treatment of FM.
**Session 4: **Relaxation training-II
**Session 5: **Strategies to increase self-esteem and regulate emotions. Pain experience and recurrent invalidation. Social support (family and friends).
**Session 6: **Relaxation training-III
**Session 7: **Holistic medicine
**Session 8: **Relaxation training-IV
**Session 9: **Benefits of physical exercise in FM. Qualitative assessment of the intervention program. Resolving doubts. Discussion concerning the strengths and weaknesses of the intervention.

In order to avoid conversations concerning the psycho-educational program among patients from different groups, we will remind the participants from the intervention of the condition that they are not allowed to talk about the program with those persons that are not attending their group. Before baseline assessment, an explanatory note addressing this important issue will be delivered to the patients participating in the program.

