### Statistical analyses

Data collected will be analysed using SAS statistical analysis software (SAS Institute Inc. 1999. v8.0, 4th ed) and employing both quantitative and qualitative techniques.

First, the intervention and control groups will be compared in order to verify that there are no significant differences between them in socio-demographic terms, clinical baseline data, etc. We shall use mean and standard deviation (SD) in continuous variables and percentages in categorical variables. For comparisons we shall use the Student-T test for continuous variables and the Chi-square test for categorical variables. Non-parametric tests may also be used.

Given that we have one between-groups factor with two levels (2 Groups: Intervention and Control) and one within-subjects factor with five levels (Baseline and 4 follow-up assessments: 0, 1, 2, 6, and 12), a 2 × 5 mixed factorial ANOVA will be performed to study the effect of the psycho-educational program on the quality of life. Then, between-subjects planned comparisons may also be used (post-hoc comparisons with independent samples T-test). If we observe differences between groups in quality of life prior to treatment, one-way analyses of covariance will be carried out using baseline scores as a covariate). In addition, we shall carry out a logistic regression analysis taking the groups as dependent variable (the target variable is a categorical variable with two categories: Intervention and Control) and the collected measures as independent variables. This analysis will let us to know the association between the intervention and the cost of the healthcare resources, controlling for the rest of variables.

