### Cost-utility analyses

Societal cost perspective will be used for the calculation of costs. *Direct costs *are going to be calculated by adding the costs derived from any medication and use of health-related services (general practitioner sessions, specialized medical sessions, emergency room sessions, and hospital in-patient stay). The cost of medications will be calculated by determining the price per milligram during the study, according to the International Vademecum (Red Book) 2007–2009, including value-added tax. Total costs of pharmacological treatment will be calculated by multiplying the price per milligram by the daily dose in milligrams and the number of days receiving such treatment. Costs derived from the use of health-related services will be calculated considering the SOIKOS unit costs database (25). *Indirect costs *will be calculated considering the days under sick leave and multiplying them by the minimum daily wage in Spain for 2007–2009. Finally, *total costs *are going to be calculated by adding direct and indirect costs.

In Spain, the National Healthcare Service (NHS) is financed by the general taxes levied by the state. In the municipalities where the study is carried out, it is administered by the autonomous government of Catalonia. Medical visits and hospital admissions are fully covered by the NHS. Medications prescribed are fully covered for retired persons, and partially for those still employed. Sick leave requires a physician's authorization, and patients unable to work continue receiving most of their salary.

When performing cost-utility analyses, two or more therapeutical options are compared in order to determine which one is the best for maximizing the benefits in light of the available resources [25,26]. This is achieved by calculating the relationship between the costs of a given intervention (e.g. A) and its consequences, expressed in QALYs, compared with another (e.g. B). This relative value is called incremental cost-utility ratio (ICUR), and it expresses the relationship between the costs and effects of one intervention compared with another.

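### Health centre is missing from the stated utility covariate list, the FIQ models and the cost model of a three-centre trial: a small, avoidable loss of precision, not a bias

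*Protocol article*

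**What the plan says.** - **Centres.** Setting and study sample opens with "Three primary health care centres (Viladecans-2, Gavà-1 and Gavà-2" and the section on Design describes individual random allocation to two arms. The article does not describe how the allocation is generated or whether it is balanced by centre.
- **FIQ.** Statistical analyses states that "a 2 × 5 mixed factorial ANOVA will be performed to study the effect of the psycho-educational program on the quality of life". The factors are group and time. Between-group t-tests may follow. If the groups differ before treatment, an ANCOVA is planned with the baseline score as its covariate.
- **Utility.** The incremental EQ-5D effects for months 0 to 6 and 6 to 12 come from least squares regressions. The covariates are listed by name: "age, gender, years of education, employment and marital status, baseline FIQ and EQ-5D utility scores, and type of medication prescribed".
- **Cost.** Twelve-month cost is to be modelled by gamma regression with a log link. That sentence gives no covariate list of its own, and it is not clear whether the list under Figure 1 is meant to cover it.
- **Physicians and care.** Data collection and ethical aspects says "Patients in the control group will receive the treatment considered most appropriate by their physician" and Cost-utility analyses says "Sick leave requires a physician's authorization". Sick-leave days make up the whole of the indirect cost as calculated.

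**The concern.** Centre is the only site factor in this design. Usual care is that of Catalan primary care, and treatment choices and sick leave both pass through a physician. It is therefore plausible, though nowhere shown, that outcomes and especially costs vary somewhat by centre. An article may leave much to a fuller plan. Here, however, it commits to a specific covariate list and to specific FIQ models, and centre is in none of them.

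Two things are at stake. Variation between centres that the other covariates do not explain stays in the residual, so intervals are wider than they need be. And if the arms happen to differ in centre mix, the estimates are not corrected for it. The planned size leaves little slack, because it gives almost exactly 80% power for the FIQ difference.

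**Working it through.** **Inputs from the article (Setting and study sample).** FIQ difference 5; SD 12.1 (the text calls it a standard error, but the stated size reproduces only if it is read as an SD); 15% dropout; 109 per arm; three centres; and, for the error rates, "assuming an alpha risk of 0.05 and a beta risk of < 0.20 in a bilateral contrast".

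**Inputs assumed.** Three centres of equal size, allocation not stratified by centre, and a centre share r of outcome variance from 0 to 0.10. The article gives none of these.

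**1. The plan's own figure.** n = 2 × (1.96 + 0.842)² × 12.1² / 5² = 91.9, so 92 evaluable per arm; 92 / 0.85 = 108.2, so 109. The stated size reproduces and does not depend on centre. With 109 × 0.85 = 92.65 evaluable per arm, power is 80.3% and the standard error of the difference is 12.1 × √(2/92.65) = 1.78 points.

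**2. Chance imbalance in centre mix.** The between-arm difference in one centre's share has SD √((1/3)(2/3)(2/109)) = 0.064, with a 95% range of about ±12.5 percentage points.

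**3. Variance with and without centre.** About 218 × 0.85 = 185 patients complete. The residual has 183 degrees of freedom without centre and 181 with it. The variance ratio is (1 − r) × 183/181:

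| r | variance ratio | interval width (square root) |
|---|---|---|
| 0 | 1.011 | 1.005 |
| 0.02 | 0.991 | 0.995 |
| 0.05 | 0.960 | 0.980 |
| 0.10 | 0.910 | 0.954 |

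Break-even is at r = 1 − 181/183 = 0.011. In the utility models r means the share that centre explains beyond the listed covariates. Those covariates use further degrees of freedom, which changes the 1% loss only slightly.

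**4. FIQ at a single time point, without baseline adjustment.** The residual SD becomes 12.1 × √(1 − r). The last column is the SD of the shift due to centre imbalance, √(2r × 12.1²/92.65).

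| r | power | n per arm incl. dropout | SE (points) | SD of shift (points) |
|---|---|---|---|---|
| 0 | 80.3% | 109 | 1.78 | 0 |
| 0.02 | 81.1% | 108 | 1.76 | 0.25 |
| 0.05 | 82.3% | 104 | 1.73 | 0.40 |
| 0.10 | 84.3% | 98 | 1.69 | 0.56 |

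The shift is not an addition to the unadjusted standard error but part of it. For r = 0.10, 1.69² + 0.56² = 3.17, against 1.78² = 3.17.

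**5. Check by simulation.** Each scenario used 20,000 trials with 93 per arm and three equal centres, and patients were allocated individually without stratification. Type I error without centre was 0.049 to 0.052 for r from 0 to 0.10. Power without and with centre was 80.3% and 79.9% (r = 0), 80.2% and 80.7% (0.02), 79.8% and 81.4% (0.05), and 79.8% and 83.5% (0.10). The gains are a little smaller than in step 4 because the simulation also pays for the 2 degrees of freedom.

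**6. Cost.** The article gives no cost SD and no centre difference, so the gain cannot be computed. As an illustration only, suppose one centre costs 10% to 40% more than the others (assumed). A one-SD imbalance then moves the cost difference by 0.064 × 0.10 to 0.064 × 0.40, or 0.6% to 2.6% of mean cost. An imbalance at the edge of the 95% range moves it by 1.3% to 5%. With an assumed coefficient of variation of 0.5 to 1.5 and 93 per arm, the standard error of the cost difference is that value × √(2/93), or about 7% to 22% of mean cost.

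**The case against.** The strongest reply is that nothing here is invalid. Randomisation makes the unadjusted comparison unbiased, chance imbalance is already inside its standard error, and the simulated type I error confirms this. That stands, and it limits the point to precision.

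The planned models also already remove part of any centre effect. In the group-by-time contrast, a centre difference that is constant over time cancels within patients, so the figures in step 4 apply to single-time-point comparisons and not to that contrast. The ANCOVA on baseline absorbs part of the effect too. The utility models already carry baseline EQ-5D, baseline FIQ, employment and type of medication. All of this stands and shrinks the gain, most of all for the FIQ.

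A reader might also infer more than the documents support:

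- **That centre differences are known.** No section reports one.
- **That each centre's own physicians decide care and sick leave.** The text speaks only of the patient's physician and of a physician's authorisation. The patients are drawn from one hospital database, and the costs include specialist, emergency and inpatient care.
- **That delivery at two of the three centres calls for a centre term.** The article says "All sessions will take place at the PC centres Gava-2 or Viladecans-2", but venue concerns only the intervention arm, and a factor for the patient's own centre does not model it.
- **That allocation is unrestricted.** The article is silent, and a condensed article may leave this to the full protocol.

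A last reply is that a centre term may itself sit in a fuller plan. That is possible for the cost model, which has no list of its own here. It is weaker for the utility regressions and the FIQ models, whose terms are stated.

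**Conclusion.** The point holds as a minor one. The stated utility covariates and FIQ models omit centre, and no section places it in the cost model. The consequence is some lost precision and an unadjusted chance imbalance, not bias and not a wrong error rate. The sample size is unaffected.

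If centre explains 2% to 10% of variance beyond the other covariates, adjustment lowers the variance to about 0.99 to 0.91 of its unadjusted value. For a single-time-point FIQ comparison this means power of about 81% to 84% in place of 80%. If centre explains less than about 1.1%, adjustment costs up to about 1% of variance. The gain, if any, lies mainly in the cost model, the utility models and the single-time-point FIQ comparisons. All of this rests on an assumed centre share, equal centres and unstratified allocation.

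**What to change.** 1. Add health centre (three levels, fixed effect) to the covariate list under Figure 1, for both utility regressions.
2. State that the list, with centre, also applies to the gamma cost model.
3. In Statistical analyses, include centre in the between-group FIQ comparisons and in the ANCOVA. The group-by-time contrast needs no change for a centre difference that is constant over time.

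The cost is 2 degrees of freedom out of about 183 in each model, at worst about 1% of variance. Each patient's centre has to be in the data set. The article lists address but not centre among its variables, so this should be confirmed. The change should be dated before outcomes are seen by arm, since a centre term added afterwards would look driven by the data.

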**Discussion:**

This research project is an attempt to demonstrate that a psycho-educational program implemented in the context of PC can produce a significant increase in the quality of life for patients with FM, as well as a decrease in the use of healthcare and social services, compared with usual care.

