Another key component in current treatment of FM is the education of patients concerning their illness [18-20]. The main objective of educational programs is to increase skills in coping and healthy behaviour on the part of patients suffering FM. Scientific evidence has demonstrated that intensive education programs (between 6 and 17 sessions) improve pain symptoms, fatigue, insomnia and quality of life. These improvements continue 3 and 12 months later [14]. Furthermore, educational programs increase patient autonomy, reducing at the same time the consumption of medicines and use of healthcare services. The total cost of the continuous use of healthcare services by FM patients has not been estimated in Spain, but data from the USA reveal an annual cost of $2,274 per patient.

To date, it has not been demonstrated in Spain whether a multimodal program, combining autogenic relaxation and active healthcare education, produces a significant improvement in the quality of life of patients with FM. In addition, we do not know whether a multimodal program is more cost-effective than the treatment usually provided to these patients.

With this background, then, the main objective of the present research project will be to determine whether a multi-component psycho-educational program for treating FM leads to better quality of life (measured with the FIQ and the EuroQol-5D) at 1, 2, 6 and 12 months, than the usual care provided in Catalan Primary Health Care. The specific aims are to assess the degree of pain perceived by fibromyalgia patients attending the multimodal program, as well as the total direct costs (medication consumption and visits to public or private healthcare professionals) and indirect (work days lost), and cost-effectiveness associated with this psychoeducational intervention, compared to usual care.

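### The bootstrap is aimed at the cost-utility ratio, which cannot be ordered if the programme is both better and cheaper; state the joint uncertainty as net benefit instead

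*Protocol article*

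**What the plan says.** In the protocol article, Cost-utility analyses, the summary that compares the two options is the ICUR, of which the article says that "it expresses the relationship between the costs and effects of one intervention compared with another". The text under Figure 1 names the method for its uncertainty: "To address uncertainty in the ICUR sampling distribution, non-parametric bootstrapping with five thousand replications will be carried out for each treatment comparison".

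Three other places bear on the sign of that ratio.
- The Discussion part of the Abstract states the hope that the programme "can produce a significant increase in the quality of life for patients with FM, as well as a decrease in the use of healthcare".
- The Background expects the same direction from programmes of this kind: "educational programs increase patient autonomy, reducing at the same time the consumption of medicines and use of healthcare services".
- Cost-utility analyses says direct costs are "calculated by adding the costs derived from any medication and use of health-related services", and total costs "are going to be calculated by adding direct and indirect costs", the indirect part being sick leave. The list contains no cost for delivering the programme, and the closing Discussion expects its outlay to be low.

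The article names no cost-effectiveness plane, acceptability curve, net benefit, value per QALY or rule for a dominant result.

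**The concern.** A ratio of cost difference to QALY difference has a usable size only when the two differences have the same sign. If the programme saves money and gains QALYs, the ratio is negative, and so is the ratio of a programme that costs more and loses QALYs. Within the favourable quadrant the size also misleads, because a larger QALY gain at the same saving moves the ratio towards zero. Near zero QALY gain the ratio jumps between large positive and large negative values.

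The result the trial hopes for is therefore one in which the sampling distribution of its chosen summary is hardest to read. At stake is how the joint uncertainty about cost and effect is stated for the second objective. If the summary is not fixed beforehand, it may end up being chosen after the quadrant is known.

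**Working it through.** **1. Reproduce the plan's own figure.** Inputs from Setting and study sample: difference 5 FIQ points, spread 12.1 (used as a standard deviation), two-sided alpha 0.05, power 0.80, dropout 15%.
- n per arm = 2 × (1.960 + 0.842)² × 12.1² / 5² = 91.9, so 92.
- 92 / 0.85 = 108.2, so 109, as stated.
- Planned standardised effect: 5 / 12.1 = 0.41. This is an FIQ effect; nothing is sized on QALYs.

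**2. Negative ratios cannot be ordered.** ICUR = ΔC / ΔE; net monetary benefit NMB = λΔE − ΔC. The ICUR column is pure arithmetic. The NMB column assumes λ = 20,000 per QALY, as the article gives no value.

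| ΔC | ΔE (QALY) | Meaning | ICUR | NMB |
|---|---|---|---|---|
| −200 | +0.02 | cheaper, better | −10,000 | +600 |
| −200 | +0.10 | cheaper, better by more | −2,000 | +2,200 |
| +200 | −0.02 | dearer, worse | −10,000 | −600 |

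Rows 1 and 3 share a ratio and have opposite meanings. Row 2 is better than row 1 and has the smaller ratio in size. NMB ranks all three correctly.

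**3. How often replicates show no QALY gain.** With 92 evaluable patients per arm and standardised QALY effect d, the expected z is d × √(92/2). Bootstrap replicates scatter around the trial's estimate, which itself scatters around the truth, so the average share at or below zero is Φ(−z/√2).
- d = 0.41 (5/12.1): z = 2.80, share 2.4%.
- d = 0.2: z = 1.36, share 16.9%.
- d = 0.1: z = 0.68, share 31.6%.

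**4. What a percentile summary of the ratio would look like.** The documents give no cost or QALY figures, so these inputs are all assumed: saving 200 (SE 250), QALY SE 0.03, normal and independent differences centred on the stated values, λ = 20,000. With SE 0.03, a gain of 0.084 gives z = 2.8 (d about 0.41), and a gain of 0.03 gives z = 1 (d = 1/√46, about 0.15).

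| | Gain 0.084 | Gain 0.03 |
|---|---|---|
| Ratio at the centre | −200/0.084 = −2,381 | −200/0.03 = −6,667 |
| 95% percentile range of the ratio | about −13,000 to +4,000 | about −90,000 to +80,000 |
| Better and cheaper | 79% | 66% |
| Better and dearer | 21% | 18% |
| Worse and cheaper | 0.2% | 12% |
| Worse and dearer | 0.05% | 3% |
| NMB, mean | 20,000 × 0.084 + 200 = 1,880 | 20,000 × 0.03 + 200 = 800 |
| NMB, SE | √(600² + 250²) = 650 | 650 |
| Share with NMB > 0 | Φ(1,880/650) = 99.8% | Φ(800/650) = 89% |

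Here 600 = 20,000 × 0.03. Quadrant shares are products of Φ(200/250) = 0.788 for cheaper and Φ(z) for better, or their complements. In both columns the ratio's range spans zero, although most draws are cheaper and better.

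**The case against.** The other side has five arguments.

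- **No interval on the ratio is promised.** True. The article speaks of addressing uncertainty in the ICUR's sampling distribution and mentions neither a percentile interval nor a decision rule based on the ratio's size. A reader might infer that the trial will end in an uninterpretable confidence interval for the ICUR; the text does not say so. What stands is that the ICUR is the named target, and any ordering of its replicates meets the problem.
- **A plane or curve may be in the full protocol or analysis plan.** Possible, and its absence from an article is not the point. The point is the target that the article does state.
- **Costs and QALYs are also modelled separately.** True: gamma regression for costs and adjusted least squares for the EQ-5D changes. A reader might infer that the trial could not say whether the programme is cost-effective. That goes too far, because these models show the direction of each difference. They do not by themselves give the joint uncertainty.
- **The negative sign is not certain.** True. The hypothesis concerns service use, not total cost. Nine two-hour group sessions cost something, and counting them could make the cost difference positive. The ratio might then be ordinary, though replicates could still cross quadrants. Net benefit serves in either case.
- **The wide range reflects a weak assumed QALY effect.** True. At an effect as large as the planned FIQ effect, the range is far narrower and draws that are worse and dearer almost vanish. The range still spans zero.

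**Conclusion.** The concern holds in a limited form. Aiming the bootstrap at the ICUR is a poor choice for a trial that expects better quality of life with less service use. The ambiguity of a negative ratio is arithmetic and needs no assumption. The size of the instability does: it is mild if QALYs respond as strongly as the FIQ is planned to, and severe if the standardised QALY effect is 0.2 or less. The ranges shown illustrate assumed inputs and do not predict this trial's results.

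Bootstrapping itself is sound, since the replicated pairs of cost and QALY differences are what a better summary needs. The FIQ comparison and the sample size of 109 per arm are unaffected. The change is worth making before the data are seen.

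**What to change.** Keep the five thousand replicates and change what is reported from them.

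1. State the joint uncertainty as incremental net monetary benefit, λΔE − ΔC, with its interval, over a pre-stated range of values per QALY.
2. Show the replicates on the cost-effectiveness plane, and give the acceptability curve over the same range.
3. Report the ICUR only as a point estimate, and only when both differences have the same sign, naming the quadrant. Otherwise report which option is dominant and give no ratio.

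The cost is a few lines of code and wording, plus the need to commit to a range of values per QALY. No new data are required.
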